### Criteria for discontinuing or modifying allocated interventions {11b}

Patients in the SMT group may be allocated to TIPS implantation according to current Baveno VII guidelines and the EASL guideline for the management of decompensated cirrhosis [1, 5, 7, 21]. TIPS implantation is indicated in the following situations:Massive variceal bleeding with implantation of a fully covered self-expanding metal stent (fcSEMS) for bleeding control (rescue TIPS implantation) [22].Variceal bleeding (esophageal or gastric varices) in patients with Child–Pugh B > 7 points and active bleeding during index gastroscopy or patients with Child–Pugh C < 14 points (pre-emptive TIPS implantation) [7].Recurrent esophageal bleeding in patients with Child–Pugh A or Child–Pugh B 7 points despite adequate secondary prophylaxis with beta-blockers and endoscopic band ligation (EBL) [7].Recurrent ascites (as defined by requirement of ≥ 3 large-volume paracenteses [removal of > 5 L of ascites] within 1 year) in stable situations can be considered for TIPS implantation. Importantly, only paracenteses in stable conditions will be considered. Stable conditions are defined as a clinical situation without concomitant infections, without acute kidney injury and/or bleeding at the time of paracentesis [1, 7].

If TIPS implantation is planned in the SMT arm, the indication should be discussed with the coordinating investigator.

### Strategies to improve adherence to interventions {11c}

The strict adherence to inclusion and exclusion criteria should improve adherence to the intervention. Further, randomisation is performed as late as possible. At each scheduled visit, the study team will reinforce the importance of treatment adherence and may help in solving upcoming problems.

### Relevant concomitant care permitted or prohibited during the trial {11d}

No medication is prohibited. Treatment with transfusions (red blood cells and platelets) and supportive care as well as intensive care treatment are permitted after the initiation of study treatment. Patients should receive treatment/medication appropriate to their clinical condition in an emergency. The patient must notify the investigational site of any new medication he/she starts taking after signature of informed consent. All concomitant medications and significant non-drug therapies (including physical therapy and blood transfusions) must be listed in the source documents and additionally documented in eCRF especially diuretic treatment, NSBB and medications for hepatic encephalopathy will be considered [23].

### Provisions for post-trial care {30}

After the patient has completed follow-up in the study, the patient will return to routine clinical practice and will receive follow-up in the outpatient clinic every 3 to 6 months according to his/her clinical condition.

All patients included in the study will have insurance in accordance with the applicable law and regulations (Insurance: Newline Group, Policy-No.: NEV081957A).

### Outcomes {12}

Table 2 summarises the objectives and the corresponding endpoints of this trial. The following estimands are defined.

**Table 2 Tab2:** Objectives and endpoints in the eTIPS trial

Objective	Endpoint
**Primary**	
The primary objective of this study is to assess a survival benefit in patients with early allocation to TIPS implantation in comparison to patients with standard medical treatment (SMT)	The primary endpoint is transplantation-free survival (TFS), defined as time from randomisation to liver transplantation or death (Estimand 1)
**Secondary**	
The secondary objectives aim to assess the efficacy of TIPS implantation on the course of liver disease and quality of life (QOL)	The following outcome parameters are defined as secondary endpoints: • Time to ascites with need for paracenteses^#^ (Estimand 2) • Quality of life assessed with the SF-36 and CLDQ (chronic liver disease questionnaire) 6 and 12 months after randomisation (Estimand 3)
**Safety**	• Adverse events (AEs), and severe adverse events (SAEs), incidence of complications related to TIPS implantation (incl. technically unsuccessful TIPS implantation) • Rate of TIPS dysfunction • Rate of TIPS implantation in the SMT group

^#^Ascites with need for paracenteses will be classified as following, taking into account the *abdominal distention* caused by ascites [1]: (I): Ascites grade 1(mild): ascites is detectable only by ultrasound examination; (II): Ascites grade 2(moderate): ascites causes moderate symmetrical distension of the abdomen; (III): Ascites grade 3 (severe, large/gross ascites): it causes marked abdominal distension. If patients develop symptoms due to ascites (pain, abdominal tension, dyspnoea), paracentesis should be performed. Date of paracentesis, volume removed and albumin replacement/dose are documented for each paracentesis. Recurrent ascites according to the Baveno VII recommendations is defined as a requirement of 3 or more large-volume (greater than 5 L) paracenteses per year (only paracenteses in stable conditions without infections are considered)[7]

#### Estimand 1

The primary estimand that corresponds to the primary trial objective to show superiority of early implantation of a TIPS in patients with liver cirrhosis and ascites compared to standard medical treatment based on the primary endpoint transplantation-free survival is specified by the following 5 attributes.

*Population:* [A] The population targeted by the primary estimand will be called full analysis set (FAS). This means that the patients will be analysed in the treatment arms to which they were randomised. All randomised patients will be included in the FAS.

*Treatments***:** The randomised experimental arm (TIPS implantation) is compared to the randomised control arm (SMT) of ascites regardless of dosing modifications, treatment interruptions, treatment discontinuation and regardless of intake of additional medications.

Treatment groups are called early TIPS and standard medical treatment.

*Variable (endpoint):* The endpoint is transplantation-free survival defined as time from randomisation to liver transplantation or death.

*Intercurrent events*: ascites, TIPS implantation and TIPS revision will be ignored.

*Population-level summary:* The population-level summary is defined by the statistical analysis approach.

### Definition of the secondary estimands

#### Estimand 2

Estimand 2 that corresponds to the secondary trial objective to assess the efficacy of TIPS implantation on the course of liver disease is specified by the following 5 attributes. *Population: [A], Treatments: [A].*

*Variable (endpoint):* The endpoint is ascites with need for paracenteses defined as time from randomisation to date of paracentesis.

*Intercurrent events*: transplantation, death will be considered as competing events.

*Population-level summary:* The population-level summary is defined by the statistical analysis approach which is described below.

#### Estimand 3

Estimand 3 that corresponds to the secondary trial objective quality of life is specified by the following 5 attributes.

*Population [B,C]:* 6, 12-month survival of FAS *Treatments:* [A].

*Variable (endpoint):* The endpoint is quality of life measured by SF-36 and CLDQ.

*Intercurrent events:* There are no intercurrent events not already addressed by the specification of population, treatments and variables.

*Population-level summary:* The population-level summary is defined by the statistical analysis approach which is described below.

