1. Patients ≥ 18 years and < 80 years. (Patients > 80 years independent of their physical constitution are excluded as they show higher complication rates and mortality after TIPS implantation) 2. Liver cirrhosis as documented by previous liver biopsy or by a combination of typical clinical, biochemical and sonographic features 3. Ascites as the first single decompensating event with grade 2 ascites and MELD ≥ 15 or grade 3 ascites [1] 4. Ability to understand the nature of the trial and the trial related procedures and to comply with them	1. Treatment refractory or recurrent ascites at the time of study inclusion 2. Patients with concomitant variceal bleeding fulfilling the criteria for pre-emptive TIPS implantation (Child–Pugh class C < 14 points or Child–Pugh class B > 7 with active bleeding at initial endoscopy or hepatic venous pressure gradient [HVPG] > 20 mmHg at the time of bleeding) 3. Budd-Chiari syndrome 4. Portal vein thrombosis (PVT) 5. Spontaneous bacterial peritonitis (SBP) 6. Uncontrolled systemic infection (defined as an increase of > 20% if inflammatory parameters [C-reactive protein, procalcitonin, leukocytes] and/or sepsis as a reason for development of ascites 7. Cardiac cirrhosis (defined as the development of liver cirrhosis in a patient with cardiac heart failure due to primary cardiac disease) 8. Clinical significant cardiac disease (NYHA ≥ II) 9. Untreated valvular heart disease: middle to high-grade valve stenosis or insufficiency (applies to mitral, tricuspid, aortic and pulmonary valves) 10. Diastolic dysfunction grade III, stated by transthoracic echocardiogram (TTE) 11. Reduced left ventricular ejection fraction ≤ 50% 12. Pulmonary hypertension (mean pulmonary arterial pressure > 45 mmHg) 13. Bilirubin > 3 mg/dl 14. Obstructive cholestasis 15. Hepatorenal syndrome type AKI 16. Acute on chronic liver failure 17. Benign liver tumor e.g. cysts within the potential puncture tract 18. Patient after liver transplantation 19. Prior TIPS implantation 20. Ongoing and/or recurrent hepatic encephalopathy (grade ≥ II) 21. Active tumor disease including hepatocellular carcinoma defined as need for chemotherapy, radiation therapy, interventional or surgical treatment 22. New onset of antiviral treatment for chronic hepatitis B virus (HBV) infection within the last 3 months 23. Untreated chronic hepatitis C virus (HCV) infection 24. Life expectancy < 1 year 25. Pregnant or breastfeeding women 26. Patients without legal capacity who are unable to understand the nature, significance and consequences of the study or who are judged as non-compliant (e.g. due to active drug abuse, severe alcohol abuse) 27. Simultaneous participation in other interventional trials which could interfere with this trial; simultaneous participation in registry and diagnostic trials is allowed 28. Person who is in a relationship of dependence/employment with the sponsor or the investigator

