## Interventions

### Explanation for the choice of comparators {6b}

Currently, TIPS implantation is recommended for patients with liver cirrhosis and refractory or recurrent ascites [1, 7]. However, response to treatment (ascites clearance) is often reduced in these patients with advanced liver disease and long-standing decompensation with ascites [13, 15]. Therefore, we hypothesise that early TIPS implantation in selected patients with ascites as the first decompensating event (grade 2 ascites and MELD ≥ 15 or grade 3 ascites) will lead to a higher rate of ascites clearance and improved transplantation-free survival. Therefore, patients with grade 2 ascites and MELD score ≥ 15 or grade 3 ascites as the first single decompensating event will be randomised in an early TIPS group in addition to standard of care and in a SMT group. Patients in the SMT group will be treated following current evidence-based treatment guidelines [1], and therefore, the SMT group reflects the current approach in treatment of patients with ascites. All patients (also including patients in the TIPS group) are advised to adhere to moderate restriction of sodium intake (80–120 mmol/day = 4.6–6.9 g of salt) according to the current EASL guidelines [1, 16]. Treatment of ascites will be performed according to current evidence-based treatment guidelines. Diuretic treatment (using an anti-mineralocorticoid drug and/or loop diuretics) will be used by clinical judgement under regular control of renal function, sodium and potassium values. The body weight loss should not exceed 0.5 kg/day in patients without peripheral oedema and 1 kg/day in the presence of peripheral oedema. The dose of diuretics can be increased after 72 h of treatment until the maximum dose (spironolactone, 400 mg/day; furosemide, 160 mg/day; torasemid, 40 mg/day) is reached or diuretic-induced complications occur [1, 16]. Diuretic-induced complications are defined as acute kidney injury (defined according the KDIGO criteria) and/or diuretic-induced hyponatraemia (decrease of serum sodium by > 10 mmol/l or to a serum sodium < 125 mmol/l) and/or diuretic-induced hypo-or hyperkalaemia (changes in serum potassium to < 3 mmol/l or > 6 mmol/l despite appropriate measures) and/or disabling muscle cramps.

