In patients with grade > 2 ascites, LVP will be performed according to current recommendations. Plasma volume expansion with albumin infusion will be performed following completion of LVP (albumin 8 g/l of ascites drained). If less than 5 l of ascites was drained, no plasma expansion is necessary [1].

The current Baveno VII guidelines make a strong recommendation for the use of non-selective beta-blockers (NSBB; preferred carvedilol or propranolol) for the prevention of decompensating events and therefore, this will be a common co-medication in the SMT group. NSBB should be stopped in case of acute kidney injury (AKI) and persistently systolic blood pressure < 90 mmHg or mean arterial pressure < 65 mmHg. After blood pressure returns to normal and AKI is resolved, NSBB can be restarted [7].

In case of development of overt hepatic encephalopathy, treatment will be started incorporating lactulose (10 ml twice or more daily as necessary) and/or rifaximin 550 mg twice daily [17].

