## Statistical methods

### Statistical methods for primary and secondary outcomes {20a}

The following populations for analyses are defined: (I) The population targeted by the primary estimand will be called full analysis set (FAS). This means that the patients will be analysed in the treatment arms to which they were randomised. All randomised patients will be included in the FAS. (II) The safety set (SAF) includes all randomised patients who underwent TIPS procedure or received SMT, and patients are analysed according to the received treatment.

The estimand and competing events are described above and summarised in Table 4.

**Table 4 Tab4:** Estimand and competing events

(Intercurrent) events	Time to	
	**Transplantation free survival**	**Ascites with need for paracenteses**
**Transplantation**	Event	Competing
**Ascites with need for paracenteses**	Ignore	Event
**Death**	Event	Competing
**TIPS implantation**	Ignore	Not available/event
**TIPS revision**	Ignore	Not available/event

The effects of SMT and TIPS implantation with respect to the primary endpoint transplantation-free survival will be estimated and tested by Cox regression. The regression model will include treatment and study site as independent variables, as well as baseline bilirubin, creatinine and age. As an estimate of the effect size, the hazard ratio between the two treatment arms will be given with the corresponding asymptotic two-sided 95% confidence interval. The two-sided test on the difference between SMT and TIPS at significance level 5% will be based on the corresponding asymptotic two-sided 95% confidence interval from the Cox regression model.

The effects of SMT and TIPS implantation with respect to the secondary endpoint time to ascites with need for paracenteses will be estimated and tested by Cox regression. The probability of event over time will be estimated by cumulative incidence rates due to competing events, transplantation and death. The time to event will be compared between the treatment groups with Cox regression models for the event-specific hazard functions using two-sided Wald tests. The regression model will include treatment and study site as independent variables, as well as baseline bilirubin, creatinine and age. As an estimate of the effect size, the event-specific hazard ratio between the two treatment arms will be given with the corresponding asymptotic two-sided 95% confidence interval.

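### The paracentesis endpoint starts at randomisation without separating drainage of the presenting ascites from re-accumulation, its one exclusion applies only before TIPS, and paracenteses after the first go unused

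*Protocol article*

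**What the plan says.** Under Definition of the secondary estimands, Estimand 2 states: "The endpoint is ascites with need for paracenteses defined as time from randomisation to date of paracentesis". It adds that "transplantation, death will be considered as competing events". No minimum time after randomisation is set, and nothing requires the ascites to have re-accumulated.

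Statistical methods {20a} fixes the model: "The time to event will be compared between the treatment groups with Cox regression models for the event-specific hazard functions using two-sided Wald tests". Each patient contributes one event. Neither Table 2 nor {20a} lists a count, a rate or a recurrent-event analysis.

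The surrounding text bears on what that event is:

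- Entry, Table 1: "Ascites as the first single decompensating event with grade 2 ascites and MELD ≥ 15 or grade 3 ascites".
- Drainage by grade, section {6b}: "In patients with grade > 2 ascites, LVP will be performed according to current recommendations".
- Drainage by symptoms, Table 2 footnote: "If patients develop symptoms due to ascites (pain, abdominal tension, dyspnoea), paracentesis should be performed".
- Intervention description {11a}: a paracentesis done to facilitate TIPS goes on the implantation page and does not count for the secondary endpoint.
- Table 3: TIPS takes place on days 1–7 after randomisation. Screening runs from day −28 to 0 with an optional paracentesis.
- Recording, Table 2 footnote: "Date of paracentesis, volume removed and albumin replacement/dose are documented for each paracentesis". Footnote 2 of Table 3 limits this after month 12 to the first paracentesis.

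**The concern.** The clock starts when every patient still has, or has just had, the ascites that made them eligible. If it is drained after randomisation, that drain is the event by definition, although it says little about what either treatment achieves later. The exclusion in {11a} removes such drains only when they precede TIPS. The same drain in an SMT patient in the same week counts.

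Two distortions follow, in opposite directions. Drains counted in both arms add early events unrelated to treatment and pull the hazard ratio towards 1. Drains counted only under SMT add early events to one arm and pull it towards TIPS, even when TIPS has no effect.

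Separately, section {6b} expects that early TIPS "will lead to a higher rate of ascites clearance and improved transplantation-free survival". With one event per patient, someone drained once and then dry contributes the same as someone drained monthly. The later paracenteses that would separate them are recorded to month 12 and enter no listed analysis.

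**Working it through.** **The plan's own figure.** The protocol gives no power or event count for this endpoint. Its only such figure is for transplantation-free survival: HR = ln 0.82 / ln 0.66 = 0.478, and 4 × (1.960 + 0.842)² / (ln 0.478)² ≈ 57.5 events, against the stated 57. That reproduces, but it does not bear on the ascites endpoint.

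**What must be assumed.** The protocol states neither paracentesis rates nor the share q of patients whose presenting ascites is drained after randomisation. Both are varied below.

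**Step 1: direction.** Take later paracenteses at 1.5 (SMT) and 0.5 (TIPS) per year, exponential, over 12 months, with no competing events. Without presenting drains the 12-month risks are 1 − e^(−1.5) = 0.777 and 1 − e^(−0.5) = 0.393. With q = 0.5 drained in about the first two weeks and counted in both arms, they become 0.5 + 0.5 × 0.777 = 0.888 and 0.5 + 0.5 × 0.393 = 0.697. Presenting drains are then about 0.5/0.888 = 56% of SMT events and 0.5/0.697 = 72% of TIPS events. Simulation gives 54% and 71%, because a few patients have another paracentesis first. Cox hazard ratios from 20,000 simulated patients per arm:

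| Share q drained after randomisation | 0 | 0.25 | 0.50 | 0.75 |
|---|---|---|---|---|
| True HR 0.33, counted in both arms | 0.33 | 0.50 | 0.65 | 0.83 |
| True HR 0.33, counted only in SMT | 0.33 | 0.26 | 0.19 | 0.13 |
| True HR 1.00, counted only in SMT | 1.00 | 0.71 | 0.50 | 0.31 |

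The exclusion in {11a} covers drains before TIPS, not those after it, so the protocol's rule lies between the two ways of counting.

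**Step 2: trial size, drains counted alike in both arms.** Inputs: 67 per arm (134/2), 12 months, follow-up ended by death or transplantation at the protocol's one-year rates of 66% and 82%, gamma frailty variance 1 (assumed), two-sided 5%, 400 trials per scenario (standard error at most √(0.25/400) = 2.5 points). The comparison is a Cox model on the first event against a rate model with robust variance on all events. The shares drained in month 1 are 0/30/60/80%.

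| Assumed rates per year, SMT vs TIPS | First-event power, % | All-event power, % |
|---|---|---|
| 3 vs 1 | 88/63/28/13 | about 99 |
| 5 vs 2 | 76/51/25/17 | about 99 |
| 1.5 vs 0.5 | 89/47/18/9 | 96–98 |
| 2 vs 1.2 | 30/18/10/7 | 54–65 |

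At 3 vs 1 the first-event hazard ratio is 0.47/0.62/0.76/0.86 and the all-event rate ratio lies between 0.34 and 0.47. The 0.47 with no presenting drains, rather than 0.33, reflects the frailty.

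**Step 3: drains counted only in SMT.** With no true effect (2 vs 2 per year) and 30% drained, the first-event HR is 0.61 with 64% false rejection. The all-event rate ratio is 0.83 with 18%. Counting all events reduces the bias but does not remove it.

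**Step 4: crossover.** Section {11b} allows TIPS under SMT for recurrent ascites (at least three large-volume paracenteses in a year). Suppose the SMT rate falls to the TIPS rate after the third paracentesis. At 5 vs 2 with no presenting drainage, the rate ratio moves from 0.40 to 0.59 and all-event power is 81–83%, level with first-event power at 82–83%. Over the range of rates tried, with 30–60% drained alike in both arms, first-event power is 11–67% against 41–100% for all events even with crossover. With drains counted only in SMT and no true effect, false rejection is 53–100% against 9–37%.

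**The case against.** Time to first paracentesis with death and transplantation as competing events is a legitimate secondary endpoint, and the background section itself describes clearance as needing no further paracenteses, which such a time can estimate. Randomisation is to be as late as possible ({11c}) and screening allows a paracentesis, so many presenting drains may precede time zero. The grade rule in {6b} does not reach grade 2 entrants, who are drained for symptoms. At q = 0 the endpoint behaves as intended. A first paracentesis also precedes any crossover triggered by recurrent ascites, which is a real reason to keep it. A supportive count could be left to a statistical analysis plan.

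All of this stands as a limit on size. It does not remove the fault in the definition: nothing requires drainage before randomisation, {11a} foresees drainage before a procedure that follows randomisation, and its exclusion has no SMT counterpart. The article itself fixes the variable, the exclusion and the model.

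Two stronger readings are not supported. A reader might infer that the endpoint measures the presenting episode instead of ascites control. That needs about half or more of patients to be drained after randomisation, which the protocol does not show. A reader might also infer that early drainage must pull the hazard ratio towards 1 and cost power. Where the exclusion in {11a} applies, the shift is the other way, towards TIPS.

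**Conclusion.** The definition should be changed. It lets drainage of the presenting ascites count as the event and handles that drain differently by arm. The resulting distortion can go in either direction. Its size depends on the share drained after randomisation, which the protocol does not give: near nil if most are drained at screening, and large under the assumed rates once a quarter or more are drained afterwards (a true HR of 0.33 read as 0.50 or 0.26, or a null effect read as 0.71).

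Leaving later paracenteses unanalysed is a lesser point. A 12-month recurrent-event analysis usually gains power and is less sensitive to the presenting drain. Power near 99% should not be expected, because that figure ignores crossover. At high paracentesis rates with little presenting drainage, the gain may vanish. Nor is every paracentesis available throughout: after month 12 only the first is recorded.

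All power and bias figures rest on assumed rates, frailty and timing. The primary analysis of transplantation-free survival and its 57 events are untouched.

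**What to change.** 1. **One rule for the presenting drain.** In Estimand 2, state for the analysis whether drainage of the presenting ascites counts, and apply the rule equally in both arms, for example through a common start point after randomisation. This defines the analysis only and does not say when patients should be drained. It is needed before the second change, since a count under the one-sided exclusion is biased too.
2. **A recurrent-event analysis to month 12, alongside time to first paracentesis.** Use the mean number or rate of paracenteses with robust variance, death and transplantation as terminal events, and patients kept in their randomised arm after rescue TIPS. Report total volume removed with it. The entry for TIPS implantation under this endpoint in Table 4 should be worded to agree.

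The cost is wording in the protocol and analysis plan. No new data or patients are needed, because each paracentesis is documented to month 12. Recruitment is planned to run to March 2028, which leaves time to amend before analysis. The drawbacks are that the added analysis stops at 12 months and that SMT crossover to TIPS dilutes its rate ratio.
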